### Interventions

Study participants will take vitamin A drops (Vitadral Aristo Pharma GmbH, Berlin, Germany) self-administered intranasally via a dropper at a dose of 10,000 IU (2 drops per nostril) once daily for 12 weeks. The dose and duration are based on the recent study by Hummel et al. [64]. All participants will receive the drops via the UEA APOLLO Research Associate once eligibility is confirmed. The participants will be taught by the research associate how to apply the drops using the Kaiteki position and a leaflet and a video will also be available for them to look at in their own time via the research team’s website (https://rhinology-group.uea.ac.uk/rhinology-and-ent-research-group). The Kaiteki position is a way of ensuring the drops roll into the olfactory cleft at the roof of the nose where the smell receptors are located [71]. Both vitamin A and peanut oil drops for the placebo arm will be received and administered in the same way.

### Arm A

Vitadral Topfen Oral Drops (Aristo Pharma) Vitadral Aristo Pharma GmbH, Berlin, Germany, to be taken daily for 12 weeks, self-administered intranasally via a dropper at a dose of 10,000 IU once daily (2 drops per nostril).

Dispensed by the research Associate after the trial participant is screened and eligibility is confirmed.

The threshold for adherence will be 80% allowing for minor interruptions (of no more than 7 days) of treatment. Participants will also be expected to take the total daily dose of 10,000 IU on at least 80% of occasions.

### Arm B

#### Matched placebo (peanut oil)

Daily application for 12 weeks. Self-administered intranasally via a dropper at a dose of 2 drops to each nostril once daily.

Dispensed by the research associate after the trial participant is screened and eligibility is confirmed.

Equivalent adherence rules will apply to both arms.

All participants will also continue to receive treatment as usual in addition to trial interventions.

### Accountability

Criteria for discontinuing or modifying allocated interventions for a given trial participant:

Patient experiencing uncomfortable side-effectsPatient develops a contraindication to MRI scanning, e.g. has a pacemaker fitted

### Compliance and adherence

Regular contact with participants by the research team will seek to ensure that they remain engaged with the study. A trial website will also provide support videos and feedback for nasal drop use. Email reminders every two weeks and follow-up phone calls to participants will aim to ensure that a minimum of 80% of the 12-week course of drops is completed and obtain feedback on any local side-effects.

### Contraindications

A combination of vitamin A and retinoic acid or its chemical derivatives (e.g. medicinal products for the treatment of skin diseases) should be avoided, as there is a risk of vitamin A overdosing.With simultaneous use of high doses of vitamin A and drugs to inhibit blood coagulation (dicumarol, warfarin), the anticoagulant effect can be increased.The simultaneous use of antibiotics such as tetracyclines and vitamin A can lead to an increase in intracranial pressure.Neomycin (an antibiotic) and cholestyramine and colestipol (medicines used to lower blood lipids) can inhibit vitamin A absorption in the intestine.Due to the already established benefit of olfactory training (OT) in PVOL [72], study participants will be asked to refrain from undertaking OT during the study period. Other intranasal treatments will also be discouraged during the study period.

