### Eligibility criteria

Adult patients presenting to ENT surgeons with symptoms of anosmia/hyposmia with or without parosmia with no conductive cause identified for their symptoms and a clear history of a preceding upper respiratory tract infection (including COVID-19) that has resolved clinically leaving the olfactory disorder.

The eligibility criteria for this trial have been carefully considered and are the standards used to ensure that only medically appropriate participants are entered. Participants not meeting the criteria should not be entered into the trial for their safety and to ensure that the trial results can be appropriately used to make future treatment decisions for other people with similar diseases or conditions. It is therefore vital that exceptions are not made to these eligibility criteria.

Participants will be considered eligible for enrolment in this trial if they fulfil all the inclusion criteria and none of the exclusion criteria as defined below.

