### Trial participant exclusion criteria

Participants with a history ofaChronic rhinosinusitis with/without nasal polyposisbSevere nasal septal deviationcMajor prior head injurydCongenital olfactory losseUse of concurrent intranasal medications or possible medications known to affect olfactionfChronic renal diseasegChronic hepatic diseasehAllergy to peanuts, soy, or vitamin A (drops contain peanut oil)Significant medical, surgical, or psychiatric disease that in the opinion of the PI would affect subject safety or influence the study outcomesCurrently taking oral vitamin A supplements, anticoagulants, or tetracyclinesAge of less than 18 or over 65Pregnant women and women of childbearing age not using an effective contraceptiveParticipants unsuitable for MRI due to metal implants, such as pacemakers, etc., as is standard for MRI scanning or who move excessively during scanning.Evidence from endoscopy or the initial MRI scan of:aParticipants with any endoscopic findings of:iChronic rhinosinusitis with/without nasal polyposisiiSevere nasal septal deviation (preventing passage of 4 mm endoscope)iiiOther inflammatory sinonasal diseasebParticipants with MRI changes indicating oedema in the sinuses and/or olfactory cleftsAny participant with a combined OBV of > 85 mm^3^ will be excluded as it is unlikely they will demonstrate a significant increase in overall volume based on previous studies of OBV [69].Participation in another trial in the last 4 months.

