### Overdose of trial medication

Hypervitaminosis is unlikely due to the topical delivery of treatment and was not evident in participants of the previous study. Therapeutic measures in the event of an overdose would be to discontinue the preparation and contact the study team.

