### Sample size

Fifty-seven participants who are eligible and have provided informed consent will be recruited and randomised on a 2:1 ratio, with 38 allocated to receive the intervention and 19 to receive placebo. This sample size will aim to detect a difference of 20 mm^3^ in OBV with 90% power based on a 2:1 allocation ratio, and based on a standard deviation of 20 mm^3^ [69] with an assumed 10% drop-out rate accounting for the above MRI-based exclusions.

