### Recruitment

Recruitment will take place over 12 months. Patients will be identified through the Smell & Taste Clinic at the James Paget University Hospital as well as from members of Fifth Sense who will be alerted via membership channels including social media and mailshots to contact the study team. Those identified from either source will be sent the relevant patient information pack (by mail/e-mail/website download). The CI and RN will screen potential participants to check their eligibility Those who contact the team via Fifth Sense will be asked to seek a GP referral to the Smell & Taste Clinic to enable recruitment. Depending on COVID-19-related restrictions at the time of commencing the study, the initial screening may be undertaken via telephone with the final eligibility checks undertaken at the baseline study visit at the UEA Brain Imaging Centre (UBIC) when they undergo their first MRI scan. In this latter scenario, the baseline Sniffin’ Sticks test will also be performed at this visit by the research associate. All necessary precautions for COVID-19 screening will be undertaken and national and local policies will be adhered to for any face-to-face contact, depending on the measures in place at the time of study commencement. Enrolment and informed consent will be undertaken by the CI and confirmed by the RA at UBIC.

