### Assignment of interventions

#### Sequence generation

Participants will be randomly assigned to either the intervention or the placebo group with a 2:1 allocation as per a computer-generated randomisation schedule. The randomisation will be performed after the initial baseline MRI scan to ensure the eligibility criteria are fully met.

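### Retinoid medicines are contraindicated with the study drug but missing from the drug exclusion criterion

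*Protocol article*

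**What the plan says.** The Contraindications section lists four drug interactions with vitamin A. The first reads: "A combination of vitamin A and retinoic acid or its chemical derivatives (e.g. medicinal products for the treatment of skin diseases) should be avoided", and the reason given is a risk of vitamin A overdose. The second is a stronger anticoagulant effect when high doses of vitamin A are taken with dicumarol or warfarin. The third is raised intracranial pressure with tetracyclines. The fourth, with neomycin, cholestyramine and colestipol, is reduced absorption of vitamin A from the gut.

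The drug item under Trial participant exclusion criteria bars people currently "taking oral vitamin A supplements, anticoagulants, or" tetracyclines. Retinoids are not named.

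The Eligibility criteria section makes the printed lists decisive: participants are "considered eligible for enrolment in this trial if they fulfil all the inclusion criteria and none of the exclusion criteria as defined below". Later steps refer back to those lists:

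- Recruitment: "The CI and RN will screen potential participants to check their eligibility".
- Sequence generation: "The randomisation will be performed after the initial baseline MRI scan to ensure the eligibility criteria are fully met".
- Interventions: "All participants will receive the drops via the UEA APOLLO Research Associate once eligibility is confirmed".

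**The concern.** The two lists do not agree. Two of the three interactions with a stated harm were carried into the exclusion criteria. The third was not, although it is the only drug combination that the Contraindications section says outright should be avoided. No reason is given for treating it differently.

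Staff who check a candidate against the criteria list could therefore enrol someone using a retinoid and supply the drops, contrary to another section of the same document. What is at stake is participant safety and consistent screening. Power, the primary analysis and the interpretation of the trial are not affected.

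Entry is also the natural place for this control. Participants and care providers are blinded, and packs are dispensed by blinded staff. They cannot apply the warning only to those allocated vitamin A. Without unblinding, the combination can be avoided only by keeping retinoid users out or by barring retinoids in both arms.

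**Working it through.** No figure in the plan needs reproducing here; the check is a comparison of text.

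**Step 1. Compare the two lists.**

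| Interaction in Contraindications | Stated consequence | Named in the drug exclusion? |
|---|---|---|
| Retinoic acid or derivatives | Vitamin A overdose; to be avoided | No |
| Dicumarol, warfarin | Stronger anticoagulant effect | Yes (anticoagulants) |
| Tetracyclines | Raised intracranial pressure | Yes |
| Neomycin, cholestyramine, colestipol | Less vitamin A absorbed | No |

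The fourth row describes no harm to the participant, so leaving it out is coherent. Of the three rows with a stated harm, 2 are excluded and 1 is not.

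**Step 2. Look for another exclusion that would cover retinoids.**

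- The vitamin A wording concerns oral supplements, not retinoid medicines.
- A separate item covers intranasal drugs and drugs known to affect smell. A skin retinoid does not clearly fall under either.
- The investigator's discretionary item concerns significant disease, not concomitant medication. It might reach someone with serious skin disease, but not every retinoid user.

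None of these clearly covers a retinoid used for skin disease.

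**Step 3. Look for a later control.** The discontinuation criteria under Accountability and under Protocol treatment discontinuation do not name retinoids. After entry, only the sentence in Contraindications applies.

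**Step 4. Exposure if a retinoid user is enrolled.** The Sample size section gives 57 participants, "with 38 allocated to receive the intervention and 19 to receive placebo".

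- Chance of allocation to vitamin A: 38 / 57 = 0.667, or 67%.
- Maximum course at one dose a day for 12 weeks: 12 × 7 = 84 doses of 10,000 IU.

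Both figures are conditional on enrolment. They do not say how many such people there would be, and the article gives no rate of retinoid use from which to work that out.

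**The case against.** The strongest reply is that the protocol already deals with the combination. It appears first in a section headed Contraindications, and a clinician who reads the whole protocol is told not to combine the drugs. For the gap to matter, the chief investigator and research nurse would have to apply the exclusion list and overlook that section. This stands as a limit on likelihood, but it does not explain the difference. Anticoagulants and tetracyclines are warned about in the same place and were still made exclusions.

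The two lists need not mirror each other. The Contraindications section also covers olfactory training and other intranasal treatments during the study, so it serves partly as on-treatment guidance. The grouping into three harmful interactions is also mine and not a category the protocol uses. Both points are fair. The exclusion list is silent on retinoids and does not permit them, so this is a mismatch and not a direct contradiction.

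The article also plays down the risk: "Hypervitaminosis is unlikely due to the topical delivery of treatment and was not evident in participants of the previous study". That limits the severity. But the reassurance rests on topical delivery of the trial product and does not address added retinoid exposure. Oral vitamin A supplements are excluded despite the same topical route.

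Finally, 67% and 84 doses simply describe the design and do not measure impact. That is correct, and they should be read only as the exposure of a retinoid user who had been enrolled.

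**Conclusion.** The concern holds as a minor safety alignment worth making. One interaction that the protocol says to avoid is absent from the criteria that control entry, while the other two with a stated harm are present. A current retinoid user satisfies the printed criteria. If enrolled, that person would have a 67% chance of up to 84 daily doses of vitamin A.

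The conclusion rests on reading the printed exclusion list as decisive, as the Eligibility criteria section says it is, and on no other item being stretched to cover retinoids. Confidence in the omission is high. How many people it would affect is unknown, and no claim is made that harm is likely. The sample size calculation and the olfactory bulb volume analysis are unaffected.

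**What to change.** Add one drug class to the existing drug item under Trial participant exclusion criteria, beside oral vitamin A supplements, anticoagulants and tetracyclines: *retinoic acid or its derivatives (systemic or topical retinoid medicines)*.

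This acts at entry. A retinoid started during the 12 weeks remains governed by the existing warning under Contraindications, which should stay.

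The cost is that a few retinoid users, topical users among them, become ineligible; the article does not allow that number to be estimated. Nothing in the sample size calculation or the analysis changes.

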### Overdose of trial medication

Hypervitaminosis is unlikely due to the topical delivery of treatment and was not evident in participants of the previous study. Therapeutic measures in the event of an overdose would be to discontinue the preparation and contact the study team.

### Protocol treatment discontinuation

In consenting to the trial, participants are consenting to trial treatments, trial follow-up, and data collection. However, an individual participant may stop treatment early or be stopped early for any of the following reasons:

Unacceptable treatment toxicity or adverse eventInter-current illness that prevents further treatmentAny change in the participant’s condition that in the clinician’s opinion justifies the discontinuation of treatmentWithdrawal of consent for treatment by the participant

As participation in the trial is entirely voluntary, the participant may choose to discontinue trial treatment at any time without penalty or loss of benefits to which they would otherwise be entitled. Although not obliged to give a reason for discontinuing their trial treatment, a reasonable effort should be made to establish this reason, whilst remaining fully respectful of the participant’s rights.

Participants who discontinue protocol treatment, for any of the above reasons, should remain in the trial for the purpose of follow-up and data analysis.

### Outcomes

**Table Taba:** 

Primary	Primary outcome measure: Olfactory bulb volume (OBV) (on MRI scan)
Secondary	• Right orbital sulcus volume (MRI scan) • Blood-oxygen-level-dependant (BOLD)-signal in primary olfactory areas; amygdala, piriform, and insula (fMRI scan) • Cerebral blood flow (CBF) in primary olfactory areas; amygdala, piriform, and insula • Psychophysical smell test (TDI) score • Olfactory disorders questionnaire (ODQ) score • Brain-derived neurotrophic factor (BDNF) (pg/ml)

### MRI scan OBV and sulcus measurements and FMRI changes

For participants in both arms of the study, MRI readings will be taken at baseline and at 12 weeks to allow for olfactory bulb measurement and the use of dynamic changes on fMRI. Each visit will be conducted in the UEA Brain Imaging Centre (UBIC) at the same time of day each time to avoid issues of circadian rhythm. Individual T1-weighted MRI images will be acquired for volumetric analyses of grey matter changes. T2-weighted BOLD imaging sequences will be acquired for analyses of functional changes in the resting state and while participants passively perceive odours (phenethyl alcohol (rose-like pleasant smell) and hydrogen sulphide (rotten eggs -unpleasant) and odourless air in repeated trials. Each stimulus will be delivered through an olfactometer for 3 s per trial, followed by a variable delay of 4–10 s after which the participant will perform a three-alternative forced-choice response indicating which odour they perceived on an MRI-compatible button box. Participants should expect to take 1.5 h for the fMRI. Additionally, diffusion tensor imaging (DTI) sequences will be deployed to investigate white matter fibre integrity and 3-min-long ASL sequence will be executed to measure cerebral blood flow. The olfactometer enables a supply of warmed odourised air flows with a delivery hose to the nose that contains no ferro-magnetic materials, thus compatible with an MRI scanner (Burghart, Wedel, Germany).

### Psychophysical smell test score and ODQ

All participants will undergo the Sniffin’ Sticks smell test at baseline (for inclusion into the study), and a repeat test will be undertaken at the 3-month visit to assess subjective olfactory performance. The smell test has 3 parts—threshold (T), discrimination (D) and identification (I); this results in a composite TDI score out of 48. The test utilises a set of pens containing odours or blanks (depending on which section of the test) and using the alternative forced choice method, participants are asked to identify the presence of the odour (threshold), the odd odour out of 3 (discrimination) or the correct odour from 4 options (identification), as the pens are waved under their nose. This test takes 20–25 min to complete. The olfactory disorders questionnaire takes about 5–10 min to complete, assesses quality of life impact, and has been previously validated by the CI in the UK setting [73].

### Brain-derived neurotrophic factor (BDNF)

See the “Non-adherence and non-retention” section below.

## Participant timeline

### Visit schedule, baseline, and follow-up assessments

#### Consent or assent

Patients will be provided with a Patient Information Sheet (PIS) and given time to read it fully. Following a discussion with a medically qualified investigator or suitable trained and authorised delegate, any questions will be satisfactorily answered and if the participant is willing to participate, written informed consent will be obtained. During the consent process, it will be made completely and unambiguously clear that the participant is free to refuse to participate in all or any aspect of the trial, at any time and for any reason, without incurring any penalty or affecting their treatment.

Consent will be re-sought if new information becomes available that affects the participant’s consent in any way. This will be documented in a revision to the patient information sheet and the participant will be asked to sign an updated consent form. These will be approved by the ethics committee prior to their use.

A copy of the approved consent form is available from the NCTU trial team.

#### Patient pathway

Patients will attend their baseline visit and then have blood samples taken for BDNF. See recruitment details below; these arrangements may depend on the influence of the COVID-19 pandemic. If necessary, in order to avoid the usual endoscopic examination, potential participants may be screened by telephone and if they do not have other rhinological symptoms (such as nasal blockage, rhinorrhoea, and facial pressure), then they will proceed into the study, with the caveat that if the subsequent MRI scan shows inflammatory sinonasal disease, they will be excluded from the study at that point and replaced with another recruit in order to achieve the planned sample size. We anticipate the chances of finding sinonasal disease after screening will be 3% or less [70], and thus may only affect 1 or 2 participants.

After completion of the baseline visit (1.5–2 h), participants will commence their nasal drops as instructed by the research team. They will be invited to reattend after 3 months for a repeat assessment. After the second visit, their participation in the study will be complete. See the flowchart below for further details.

#### Early stopping of follow-up

If a participant chooses to discontinue their trial treatment, they should continue to be followed up as closely as possible to the follow-up schedule defined in the protocol, providing they are willing. They should be encouraged and facilitated not to leave the whole trial, even though they no longer take the trial treatment. If, however, the participant exercises the view that they no longer wish to be followed up, this view must be respected, and the participant must withdraw entirely from the trial. NCTU should be informed of the withdrawal in writing using the appropriate APOLLO trial documentation. Data already collected will be kept and included in analyses according to the intention-to-treat principle for all participants who stop follow-up early. Participants who stop trial follow-up early will be replaced (but their data utilised unless they request withdrawal of data).

#### Loss to follow-up

Participants who are lost to follow-up (despite attempts to contact them on 3 occasions), will be withdrawn from the study.

